# Dexamethasone-Induced Sarcopenia and Physical Frailty in Children With Acute Lymphoblastic Leukemia: Protocol for a Prospective Cohort Study

**DOI:** 10.2196/33517

**Published:** 2022-04-11

**Keywords:** acute lymphoblastic leukemia, sarcopenia, physical frailty, muscle atrophy, dexamethasone, fatigue, physical activity, glucocorticoid-induced atrophy

## Abstract

**Background:**

During treatment for pediatric acute lymphoblastic leukemia (ALL), children receive high doses of dexamethasone for its apoptotic effect on leukemia cells; however, muscle atrophy is a well-known serious side effect. Muscle atrophy (loss of muscle mass) accompanied by a decreased muscle strength may lead to a generalized impaired skeletal muscle state called sarcopenia. Loss of muscle mass is also an indicator of physical frailty, which is defined as a state of increased vulnerability that is characterized by co-occurrence of low muscle mass, muscle weakness, fatigue, slow walking speed, and low physical activity. Both sarcopenia and physical frailty are related to an increased risk of infections, hospitalizations, and decreased survival in children with chronic diseases.

**Objective:**

This study aims to (1) estimate the occurrence of sarcopenia and physical frailty in children during ALL maintenance therapy, (2) evaluate the effect of administering dexamethasone, and (3) explore determinants associated with these outcomes.

**Methods:**

This prospective study is being pursued within the framework of the DexaDays-2 study: a randomized controlled trial on neurobehavioral side effects in pediatric patients with ALL. A total of 105 children (3-18 years) undergoing ALL maintenance treatment at the Princess Máxima Center for Pediatric Oncology are included in this study. Sarcopenia/frailty assessments are performed before and just after a 5-day dexamethasone course. A subset of 50 children participating in the DexaDays-2 trial because of severe dexamethasone-induced neurobehavioral problems were assessed at 3 additional timepoints. The sarcopenia/frailty assessment consists of bioimpedance analysis (skeletal muscle mass [SMM]), handheld dynamometry (handgrip strength), Pediatric Quality of Life Inventory Multidimensional Fatigue Scale (fatigue), Timed Up and Go Test (TUG; walking speed), and physical activity questionnaires. To evaluate potential change in sarcopenia/frailty components after a 5-day dexamethasone administration, a paired Student t test or Mann-Whitney U test will be used. Because of the presence of repeated measurements, generalized linear mixed models will be used to estimate the effect of dexamethasone on sarcopenia and frailty outcomes. Multivariable regression models will be estimated to investigate associations between the assessment scores and patient and treatment-related factors.

**Results:**

Patient accrual started in 2018 and was finalized in spring 2021. From autumn 2021 onward final data analyses will be performed.

**Conclusions:**

This first study combining parameters of sarcopenia and physical frailty is of importance because these conditions can seriously complicate continuation of ALL therapy, independence in physical functioning, reaching motor milestones, and participating in daily life activities. The results will provide knowledge about these complications, the association between dexamethasone treatment and muscle loss and other components of frailty, and therefore insights into the severity of this side effect. By exploring potential determinants that may be associated with sarcopenia and physical frailty, we may be able to identify children at risk at an earlier stage and provide timely interventions.

**International Registered Report Identifier (IRRID):**

DERR1-10.2196/33517

## Introduction

Acute lymphoblastic leukemia (ALL) is the most prevalent pediatric cancer worldwide. Advances in treatment strategies and supportive care have resulted in a 5-year survival rate of about 90% in high-income countries [1-3]. Consequently, there is growing attention for adverse health effects, including impairments in physical performance during and after therapy [4-6]. Impairments in physical performance, either transient or permanent, in children with ALL are usually explained by a neurological disorder, fractures, osteonecrosis, general malaise, pain, or severe muscle atrophy [7-11]. Muscle atrophy, in turn, can be caused by malnutrition, inflammation, low physical activity, and can be aggravated by treatment with glucocorticoids [12,13]. Glucocorticoids, which are essential in the treatment of ALL, are known to regulate protein metabolism in skeletal muscle, thereby inducing a catabolic effect and consequent muscle atrophy [14,15].

Dexamethasone is the most potent glucocorticoid and a cornerstone for the treatment of pediatric ALL, because it reduces the frequency of central nervous system relapse [15]. As it is administered in high doses for considerable periods in various ALL protocols worldwide (6 mg/m^2^ per day) [16-18], children with ALL carry an increased risk of glucocorticoid-induced muscle atrophy [15].

Muscle atrophy (loss of muscle mass) when accompanied by decreased muscle strength may indicate a generalized skeletal muscle disorder called sarcopenia [19]. Sarcopenia, defined as the combination of low muscle mass and strength or function, is associated with increased adverse health outcomes in various adult populations [20]. The presence of sarcopenia has been investigated to a limited extent in 3 previous studies including children with ALL [4,21,22], which indicated that muscle mass loss in children during ALL therapy was associated with the number and duration of hospital admissions [4], occurrence of invasive fungal infections, other adverse events of Common Terminology Criteria for Adverse Events (CTCAE) grade ≥III [21], and even—when fat mass and body mass index were increased—with impaired survival [22]. However, due to small sample sizes and methodological limitations, which make it difficult to correct for relevant confounders, it is unclear if these results indicate a true causal relationship or coassociation.

Physical frailty is another undesired consequential state, and is characterized by 5 components: unintentional weight loss (due to muscle mass loss), muscle weakness, self-reported exhaustion, slow walking speed, and low physical activity [23]. Physical frailty has been reported as a state of reduced physiologic reserve with increased vulnerability to stressors. It was first defined in the elderly by Fried et al [23], and was shown to be associated with disabilities and early mortality in young adult survivors of childhood cancer [24-27]. The 5 components of physical frailty have all been individually described to occur in children with ALL. For example, higher levels of fatigue were reported in children with ALL compared with children from the general population, and more often during dexamethasone treatment [28,29]. Besides, several studies showed that children with ALL had muscle mass loss [22], muscle weakness [5,6,30], slow walking speed [5,31], and reduced physical activity levels [32-34]. It is therefore relevant to study whether co-occurrence of these 5 physical frailty components may be prevalent in children with ALL, putting them at risk for serious complications.

There is some known overlap between physical frailty and sarcopenia; in fact, sarcopenia has been reported as a precursor of frailty in older adults [23,35-37]. The biological and clinical relationships between these 2 states in pediatric cancer populations are not clear yet.

The development of sarcopenia or physical frailty or both in children during ALL therapy is undesirable because of the consequences it may have for therapy (discontinuation or dose reduction due to clinical state), physical abilities, motor development, and child participation levels in daily life activities, as well as the potential negative effects on the longer term. To our knowledge, physical frailty in children has been assessed in only 2 previous studies, but not yet in pediatric patients with cancer. In both studies the frailty phenotype was associated with severe infections and increased hospitalizations [38,39].

So far, frailty has not been examined in children during ALL treatment nor has the relationship between dexamethasone and sarcopenia/frailty been investigated. Hence, the aims of this study are to estimate the occurrence of sarcopenia and physical frailty in children with ALL during maintenance therapy, to evaluate the effect of administering dexamethasone on sarcopenia and frailty (and their individual components) and to explore potential determinants associated with these outcomes. This paper describes the statistical design and methodology for this study.

## Methods

### Study Design and Patient Recruitment

This prospective national observational cohort study is taking place at the Princess Máxima Center for Pediatric Oncology, Utrecht, the Netherlands. The children included in this study are participating in the DexaDays-2 study: a randomized controlled trial on neurobehavioral side effects in pediatric patients with ALL [40]. In that study, Dutch patients with ALL are eligible when they fulfill the following criteria: age 3-18, confirmed diagnosis of ALL, and inclusion in the Dutch Childhood Oncology Group (DCOG) medium-risk group of the ALL-11 protocol. Only patients between 3 and 18 years can participate as this was an inclusion criterion for the DexaDays-2 study, because the questionnaires used in that study are validated only for those ages. Children who reach the age of 3 years during maintenance therapy and are still due to receive 5 dexamethasone courses after their birthday (at least 15 weeks before the end of therapy) are also eligible. Exclusion criteria of that study are anticipated compliance problems, underlying conditions that affect the absorption of oral medication, uncontrolled infections, or any other complications that may interfere with administering dexamethasone treatment, insufficient command of the Dutch language, preexisting mental retardation, and hydrocortisone or risperidone use during the invitation to participate.

Our study on sarcopenia and frailty is being pursued within the framework of the aforementioned DexaDays-2 study. The latter consists of 2 parts: an identification study (including 2 timepoints: T1-T2) and a randomized controlled trial (T3-T11). The prospective observations of the current study are performed at a subset of these time points (Figure 1) during 15 weeks of the maintenance phase of ALL therapy.

A total of 105 patients will undergo a physical frailty assessment before (T1) and after 5 days (T2) of dexamethasone administration (6 mg/m^2^ per day in 3 dosages). A subset of 50 children will be assessed at 3 additional timepoints (T3, T7, and T11), to observe the process of sarcopenia and physical frailty longitudinally. This subset comprised children participating in the DexaDays-2 randomized controlled trial based on the severity of their neurobehavioral problems. These 50 patients will receive physiological dosages of hydrocortisone or placebo during a 5-day dexamethasone treatment, and the cross-over will take place after 2 courses of dexamethasone treatment. The sample size is based on the DexaDays-2 study power calculation [40].

**Figure 1 figure1:**
[figure not shown]
Timeline for sarcopenia and physical frailty assessment during the study. ^a^Patients continue with this part of the study when they have significant dexamethasone-induced behavioral problems, based on the study design of the DexaDays-2 study. ALL: acute lymphoblastic leukemia; MR: medium risk; Dexa: dexamethasone.

### Ethics Approval

The study was approved by the Medical Ethics Committees of the Erasmus Medical Center Rotterdam (reference number: NL62388.078.174).

### Outcome Definitions: Sarcopenia and Physical Frailty

#### Sarcopenia

We will use the most widely cited definition of sarcopenia as proposed by the European Working Group on Sarcopenia [19,39], that is, the combination of low muscle strength or function, and impaired muscle mass [19]. For decades, the term sarcopenia had been used to describe muscle loss alone without reference to function. However, recent updates and consensus definitions state the importance of including muscle function in the concept of sarcopenia [39]. Therefore, in this study, sarcopenia is defined as a combination of impaired muscle mass and low muscle strength.

These components are also separately included in the frailty definition (Table 1, Figure 2).

**Table 1 table1:** Short overview of definition and measurements used to assess sarcopenia in children with ALL^a^.

EWGSOP^b^ sarcopenia definition	Concept used in previous pediatric ALL studies	Method used in our study
Loss of muscle mass	Psoas muscle area loss evaluated using computed tomography [20]. Skeletal muscle mass or lean body mass evaluated using dual-energy X-ray absorptiometry [4,21].	Skeletal muscle mass evaluation by bioimpedance analysis.
Muscle weakness	N/A^c^	Handgrip strength evaluation using handheld dynamometry.

^a^ALL: acute lymphoblastic leukemia.

^b^EWGSOP: European Working Group on Sarcopenia in Older People.

^c^NA: not applicable.

**Figure 2 figure2:**
[figure not shown]
Physical frailty and sarcopenia definitions and the individual components.

#### Physical Frailty

In accordance with the original definition of Fried et al [23] and previous clinical frailty studies in childhood cancer survivors, we will define frailty using the following components: low muscle mass, muscle weakness, self-reported fatigue, slow walking speed, and low physical activity [24,25]. Prefrailty and frailty will be defined, respectively, by the presence of 2, or 3 or more of the 5 components [22]. Assessments are excluded if 3 or more components are missing.

The outcome measures to examine sarcopenia and physical frailty components are selected based on suitability for children with an age range of 3-18 years (Table 2).

**Table 2 table2:** Short overview of measurements used to assess frailty in childhood cancer survivors and in this study.

Frailty components	Concept used in CCS^a^	Method used in the current study in children with ALL^b^
Shrinking/weight loss	Lean muscle mass evaluated using DXA^c^ [24,25].	Skeletal muscle mass evaluation by bioimpedance analysis.
Weakness	Handgrip strength evaluated using handheld dynamometry [24,25].	Handgrip strength evaluation using handheld dynamometry.
Exhaustion	Self-reported exhaustion assessed using the SF-36^d^ [25] or during a semistructured interview [24].	Self-reported fatigue assessment using PedsQL-MFS^e^.
Slowness	Slow walking speed evaluated based on cut-off points for 15 ft [25], or by using the 6-Minute Walk Test [24].	Slow walking speed evaluation using the Timed Up and Go Test.
Low physical activity	Energy expenditure during leisure time physical activity based on the NHANES^f^ Physical Activity [25] and based on frequency and duration per week derived from a semistructured interview [24].	Energy expenditure evaluation based on physical activity questionnaires.

^a^CCS: childhood cancer survivors.

^b^ALL: acute lymphoblastic leukemia.

^c^DXA: dual x-ray absorptiometry.

^d^SF-36: 36-item Short Form Survey.

^e^PedsQL-MFS: Pediatric Quality of Life-Multidimensional Fatigue Scale.

^f^NHANES: National Health and Nutrition Examination Survey.

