#### Muscle Strength

Handgrip strength (kilogram) will be measured in sitting position with the elbow flexed at 90° using a hydraulic Jamar handheld dynamometer (Sammons Preston). During the measurement the child will be verbally encouraged to achieve a maximum performance. For both the dominant and nondominant hand the mean score of 3 repeats will be calculated. Raw results will be compared with population-based age- and sex-specific reference values [44]. Handgrip dynamometry showed good validity (intraclass correlation coefficients [ICCs] 0.73-0.91) with high reproducibility in children from the age of 4 years and has excellent test-retest reliability (ICC 0.91-0.93) [45,46], and the measurement was feasible in children with leukemia [47].

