#### Fatigue

Fatigue-related complaints will be assessed using the validated Dutch version of the Pediatric Quality of Life Inventory (PedsQL)-Multidimensional Fatigue Scale (MFS) [48,49]. This questionnaire consists of 3 scales: General Fatigue, Sleep/Rest Fatigue, and Cognitive Fatigue, resulting in subscores and in a total fatigue score. We will use parent proxy reports for children aged 2-4, 5-7, 8-12, and 13-18 years, as well as self-report versions for children aged 8-12 and 13-18 years. The results of PedsQL-MFS will be compared with Dutch normative values from the general population [48]. The internal consistency of the Dutch version of the PedsQL-MFS has been reported as satisfactory (Cronbach coefficient α >.70), test-retest reliability was good (ICC 0.68-0.84), and the interobserver reliability varied from moderate to excellent (ICC 0.56-0.93) [48]. The original version of PedsQL-MFS has been validated in patients with pediatric cancer, 50% of whom had ALL [49], and the Dutch version has been used previously in studies in children with ALL [28,50].

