### Statistical Analysis

The results of the physical frailty assessments, that is, SMI, handgrip strength, self-reported fatigue, walking speed, and physical activity (component scores), will be reported as means and SDs, or as median and interquartile ranges if data are non-normally distributed. The frequency of sarcopenia and physical frailty, as well as the individual components at all timepoints will be reported in percentages and schematically visualized. A correlation matrix will be built to explore coherence between the additional measure TRF and the other frailty components.

To evaluate the potential change in frailty components after 5 days of dexamethasone administration, a paired Student *t* test or Mann-Whitney *U* test will be used depending on the distribution of the data.

To evaluate whether the mean scores from the frailty components change between T1, T3, T7, and T11, 1-way ANOVA will be employed.

To study the effect of dexamethasone administration at T1, T3, T7, and prior to T11 on sarcopenia, physical frailty, and each individual components, generalized mixed models will be estimated. These models incorporate correlations between repeated responses on the same individual. Patient-specific random intercept, age, weight, time since the start of therapy, and cumulative vincristine dosage will be included in the model.

Multivariable linear regression model will be estimated to investigate associations between the potential determinants (patient- and treatment-related factors, pharmacokinetics, and genetics) and the assessment scores at T1 and T2 (SMI, handgrip strength, self-reported fatigue, walking speed, TRF, and physical activity). Results will be presented as regression coefficients along with 95% CI.

Multivariable logistic regression models will be estimated to explore associations between the aforementioned potential determinants and the occurrence of sarcopenia and physical frailty at T1 and T2. Odds ratios along with 95% CIs will be estimated.

Statistical analyses will be performed using software packages R Statistics (version 1.0.143; R Foundation) and SPSS (version 26.0.0.1) for Windows (IBM).

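### Frailty is scored against fixed counts of 2 and 3 even when one or two of the five components are missing, so frailty can only be under-counted

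*Protocol article*

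**What the plan says.** The Physical Frailty section of the protocol article lists five components and sets the categories by absolute count: "Prefrailty and frailty will be defined, respectively, by the presence of 2, or 3 or more of the 5 components". The next sentence is the only rule for incomplete data: "Assessments are excluded if 3 or more components are missing". Assessments with one or two missing components therefore stay in.

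Neither that section nor Statistical Analysis prorates the cut-off, imputes a missing component or provides an undetermined category.

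Frailty status then feeds three analyses in Statistical Analysis:
- the descriptive report: "The frequency of sarcopenia and physical frailty, as well as the individual components at all timepoints will be reported in percentages";
- the generalized mixed models for the effect of dexamethasone;
- the logistic models for determinants of "the occurrence of sarcopenia and physical frailty at T1 and T2".

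The number assessed is given in Study Design and Patient Recruitment: "A total of 105 patients will undergo a physical frailty assessment before (T1) and after 5 days (T2) of dexamethasone administration".

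**The concern.** A child with all five components measured is frail if any three are impaired. A child with three measured must be impaired on every one. The threshold is the same, but the number of chances to reach it is not. The article never says that a missing component is taken as normal; that follows from comparing a count of observed impairments with a fixed number.

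At stake is the occurrence of frailty, which is the first aim. The mixed and logistic models use the same status. Any missingness that differed by visit or by a determinant would therefore enter them as an apparent effect.

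**Working it through.** The article gives no frailty rate, component prevalence or missing-data rate, so there is no stated figure to reproduce. From the document: 5 components, cut-offs 2 and 3, exclusion at 3 or more missing, 105 children at T1 and T2. Assumed: component prevalence p, correlation ρ between components, the shares with one or two missing, and missingness unrelated to impairment.

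**Step 1. Direction.** Deleting a component cannot raise the number of observed impairments. The proportions with at least 3 and with at least 2 can only fall. The proportion with exactly 2 gains children who drop from 3 or more and loses children who drop to 1 or 0, so its sign is open.

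**Step 2. Loss for one child.** Let k of 5 components be truly impaired.
- k = 3, one missing: still frail only if the missing one is among the 2 unimpaired, 2/5 = 0.40.
- k = 3, two missing: both must be the 2 unimpaired, 1/C(5,2) = 1/10 = 0.10.
- k = 4, one missing: always still frail. Two missing: the pair must include the single unimpaired component, 4/10 = 0.40.
- k = 5: always still frail.

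**Step 3. Rate by number measured (m).** With independent components, P(frail | m) = P(Binomial(m, p) ≥ 3). With correlation, a latent normal model gives q(z) = Φ[(Φ⁻¹(p) + √ρ·z)/√(1−ρ)], and P(Binomial(m, q(z)) ≥ 3) is averaged over a standard normal z.

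| p | ρ | m = 5 | m = 4 | m = 3 |
|---|---|---|---|---|
| 0.2 | 0 | 5.8% | 2.7% | 0.8% |
| 0.3 | 0 | 16.3% | 8.4% | 2.7% |
| 0.3 | 0.3 | 22.9% | 14.9% | 6.6% |
| 0.4 | 0 | 31.7% | 17.9% | 6.4% |

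Over p = 0.2, 0.3, 0.4 and ρ = 0, 0.3, 0.5, the ratio to the five-component rate is about 47-76% for m = 4 and 14-45% for m = 3. A beta-binomial model (p = 0.3, correlation 0.3) gives 25.6%, 18.3% and 9.5%, that is 71% and 37%, inside those ranges.

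**Step 4. Whole cohort.** Loss = a₁(P₅ − P₄) + a₂(P₅ − P₃), where a₁ and a₂ are the shares missing one and two components.
- 5%/2%, p = 0.2, ρ = 0: 0.05 × 3.1 + 0.02 × 5.0 ≈ 0.25 points.
- 5%/2%, p = 0.3, ρ = 0.3: 0.05 × 8.0 + 0.02 × 16.3 ≈ 0.73 points, or 0.8 of a child in 105.
- 5%/2%, p = 0.4, ρ = 0: 0.05 × 13.8 + 0.02 × 25.3 ≈ 1.2 points, or 1.3 children. This is the largest loss on the grid.
- 20%/10%, p = 0.3, ρ = 0: 0.20 × 7.9 + 0.10 × 13.6 ≈ 2.9 points, about 14.0 children scored frail instead of 17.1 (−18%).

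**Step 5. Prefrail share, independent components.** At p = 0.3 it falls from 30.9% (m = 5) to 26.5% (m = 4) and 18.9% (m = 3). At p = 0.5 it rises from 31.3% to 37.5% for both.

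**Step 6. Unequal missingness between visits, with no true change.** If T1 has 5%/2% and T2 has 20%/10%, the extra 15%/8% gives a false fall of 0.15 × 3.1 + 0.08 × 5.0 ≈ 0.9 points up to 0.15 × 13.8 + 0.08 × 25.3 ≈ 4.1 points. With 8%/3% at T2 the false fall is 0.1 to 0.7 points. Both contrasts are hypothetical.

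**The case against.** The strongest reply is about size. The ratios in step 3 apply only to incomplete assessments. At 5%/2% missingness the cohort loses about one child in 105 or fewer. The sampling standard error of a 22.9% prevalence is √(0.229 × 0.771/105) ≈ 4.1 points. This stands: a material bias is possible but not shown.

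A second reply is that the article sets only a minimum-data rule and that a fuller plan may impute or add sensitivity analyses. It may. But the stated rule can be followed as it is, and followed as it is, it gives a biased count.

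A reader might also infer more than the documents support:
- **That young children lack components, so the age coefficient is biased.** The Fatigue section does list "self-report versions for children aged 8-12 and 13-18 years", but the same sentence provides parent-proxy forms for every eligible age. Activity is also proxy-reported from age 3. For grip, "with high reproducibility in children from the age of 4 years" describes cited reproducibility; it does not say that grip goes unmeasured below 4, and it concerns 3-year-olds at most.
- **That T2 has more missing data and so hides harm from dexamethasone.** Nothing in the article indicates this. The paired T1-T2 test is on the component scores and is untouched by the cut-off.
- **That the exclusion also removes usable sarcopenia data.** The sentence stands under the frailty heading, directly after the frailty cut-off, and sarcopenia has its own section. The natural reading confines it to frailty.

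**Conclusion.** The point holds as a defect of the stated scoring rule. The direction is certain for frailty, and the prefrail category can move either way. The size is conditional: about 0.25 to 1.2 percentage points for the whole cohort at 5%/2% missingness and more as missingness rises, given component prevalence of 20-40%, correlation of 0-0.5 and missingness unrelated to impairment. If components were missing because the child was too impaired to be tested, the loss would be greater. Missingness that differed by visit or by a determinant would distort the mixed and logistic models of frailty status, but the article does not show that such a difference exists. The rule should be fixed before analysis; on this evidence it does not threaten the study's conclusions.

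**What to change.** Replace the scoring rule in Physical Frailty as follows.
- **Frail:** at least 3 measured components are positive.
- **Not frail:** positives plus missing are fewer than 3.
- **Otherwise:** undetermined. This covers two positives of four measured, and one or two positives of three measured.
- **Prefrailty:** apply the same logic at 2. At least two is settled when 2 or more measured components are positive, and ruled out when positives plus missing are fewer than 2. Exactly two is therefore settled only in a complete assessment.

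For undetermined assessments, multiply impute the missing components from the other components, age, sex and the child's other visit. Beside the imputed result, report the lower bound (all missing taken as normal) and upper bound (all missing taken as impaired) for the proportions with at least 3 and at least 2 components. Also report the number of components missing at each visit, so that readers can judge whether missingness differs.

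The cost is a few sentences and a short extra analysis step. No new data are needed. The downside is that some assessments will carry the label undetermined.

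### Frailty assessments with one or two missing components are kept under an unchanged 3-of-5 cut-off, so on the plain reading frailty can only be under-counted in them

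*Protocol article*

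**What the plan says.** The Physical Frailty section fixes the cut-offs on a count out of five: "Prefrailty and frailty will be defined, respectively, by the presence of 2, or 3 or more of the 5 components". The five components are muscle mass, grip strength, fatigue, walking speed and physical activity. The rule for incomplete data follows directly: "Assessments are excluded if 3 or more components are missing". By implication, an assessment with one or two components missing is kept. The article gives no imputation, rescaling, bounds or complete-case rule for those assessments.

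The classification matters for the first objective, which is to "estimate the occurrence of sarcopenia and physical frailty in children during ALL maintenance therapy". The Statistical Analysis section says how this is reported: "The frequency of sarcopenia and physical frailty, as well as the individual components at all timepoints will be reported in percentages". The same frailty status is the outcome of the logistic models at T1 and T2, and one of the outcomes of the generalized mixed models.

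One component also has an unclear source. The Physical Frailty section and Table 2 call it self-reported fatigue. The Fatigue section collects parent proxy reports at every age, "as well as self-report versions for children aged 8-12 and 13-18 years". No self-report is collected at ages 3-7, and the article does not say which score defines the component at any age.

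**The concern.** The cut-off of three assumes that five components were looked at. If only four or three were, a child has fewer chances to reach three. A child with two components missing is frail only if all three observed ones are abnormal.

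The error has one direction. Counting a missing component as not present can move a child from frail to prefrail or non-frail, or from prefrail to non-frail, but never upward. The percentage frail, and the percentage at least prefrail, can therefore only be too low. The percentage exactly prefrail can move either way, because it loses children to non-frail and gains them from frail.

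Two things are at stake. The first is the frailty half of the first objective. The second is comparison between groups and visits: if completeness differs by age or timepoint, part of any difference in frailty percentage, or of an age coefficient in the models, would reflect completeness.

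**Working it through.** **Inputs from the article.** Cut-offs of 3 and 2 out of 5, and exclusion only from three missing upward (Physical Frailty); 105 children at T1 and T2 (Study Design and Patient Recruitment). The article gives no expected frailty rate and no missing-data rate, so there is no stated figure to reproduce.

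**Assumptions.** Each component is abnormal with probability p between 0.2 and 0.5. Components are independent, or correlated within a child at 0.3 (beta-binomial). A missing component counts as not present.

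**Step 1: detected frailty by number observed.** With k components observed, detected frailty is P(X ≥ 3), X ~ Binomial(k, p). At p = 0.3:

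- k = 5: 10(0.3³)(0.7²) + 5(0.3⁴)(0.7) + 0.3⁵ = 0.1323 + 0.0284 + 0.0024 = 16.3%
- k = 4: 4(0.3³)(0.7) + 0.3⁴ = 0.0756 + 0.0081 = 8.4%
- k = 3: 0.3³ = 2.7%

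**Step 2: effect on the overall percentage.** Overall = (1 − a − b)·P₅ + a·P₄ + b·P₃, where a and b are the shares of assessments with one and two components missing at random. The mixes are assumed: A is a = 10%, b = 0; B is 10% and 10%; C is 20% and 10%.

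| p | 5 observed | 4 observed | 3 observed | Mix A | Mix B | Mix C |
|---|---|---|---|---|---|---|
| 0.2 | 5.8% | 2.7% | 0.8% | 5.5% | 5.0% | 4.7% |
| 0.3 | 16.3% | 8.4% | 2.7% | 15.5% | 14.2% | 13.4% |
| 0.4 | 31.7% | 17.9% | 6.4% | 30.4% | 27.8% | 26.4% |
| 0.5 | 50.0% | 31.2% | 12.5% | 48.1% | 44.4% | 42.5% |
| 0.3, correlation 0.3 | 25.6% | 18.3% | 9.5% | 24.8% | 23.2% | 22.5% |

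At p = 0.3 the shift is about 1 to 3 points, with or without correlation. In mix C with independence it is about 17 of 105 children falling to about 14. Across the independent rows it runs from 0.3 points (p = 0.2, mix A) to 7.5 points (p = 0.5, mix C).

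**Step 3: comparison with sampling error.** At 16% and n = 105, the 95% half-width is 1.96·√(0.16 × 0.84 / 105) = 7.0 points.

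**Step 4: if missingness is informative.** Suppose the missing components are always abnormal in truth, with p = 0.3 for the observed ones. With one missing, true frailty is P(X ≥ 2 of 4) = 34.8% against 8.4% scored. With two missing it is P(X ≥ 1 of 3) = 65.7% against 2.7% scored.

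**Step 5: the prefrail category.** P(X = 2) for five, four and three observed is 30.9%, 26.5% and 18.9% at p = 0.3, but 31.3%, 37.5% and 37.5% at p = 0.5. So the exactly-prefrail percentage can fall or rise, while the percentage with two or more always falls (47.2%, 34.8%, 21.6% at p = 0.3).

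**Step 6: simpler repairs.** These are at p = 0.3 with independence.

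- *Pro-rating at 60% of the observed components.* The cut-off stays at 3 with four observed (8.4%) and drops to 2 with three observed (21.6%, above the true 16.3%). It is wrong in opposite directions.
- *Classifying only when the missing components cannot change the three-way category.* With one missing, counts of 1 or 2 are unsettled: 41.2% + 26.5% = 67.6%. With two missing, every count except 3 is unsettled: 97.3%. Most incomplete assessments would be lost.

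**The case against.** The strongest reply is that the article says when an assessment is excluded, not that a missing component counts as normal. A condensed article may leave the scoring of retained assessments to a full protocol or analysis plan, which could impute or give bounds. This stands in part: the bias is conditional on the plain reading. But the article states its own missing-component rule beside a fixed count out of five, and following the two as written gives the downward error. The objection is to what is fixed, not to missing detail.

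Several stronger readings are tempting, and the documents do not support them:

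- *That the loss is greatest in the youngest and weakest children.* The article has no missingness data. It is plausible for the standing, grip and walking tests: muscle mass is measured standing, and grip is cited as having "high reproducibility in children from the age of 4 years" while 3-year-olds are enrolled. But that citation concerns measurement quality, not missingness, and the article calls grip and the Timed Up and Go Test feasible in children with leukemia.
- *That fatigue is structurally missing at ages 3-7.* Parent proxy reports are collected at all ages, and parent-reported activity covers ages 3-11. The conflict is in the label.
- *That being unable to rise from the floor lowers the count.* The rise test is an exploratory addition and not one of the five components.
- *That overall frailty is cut by half or more.* Losses of that size apply only within incomplete assessments.
- *That the T1-T2 tests are distorted.* The paired tests use component scores, which this rule does not touch. Only frailty percentages and models of frailty status are exposed.
- *That this is the study's main estimate.* No primary endpoint is named, and sarcopenia, which does not use this rule, shares the first objective.

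**Conclusion.** The point holds in a limited form. The rule keeps incomplete assessments under a cut-off meant for five components. If missing counts as not present, the percentage frail and the percentage at least prefrail are biased downward, never upward.

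Within incomplete assessments the relative loss is large. Over p = 0.2-0.5 with independent components, detected frailty is 0.47-0.62 of its true value with one missing and 0.14-0.25 with two. With correlation 0.3 the ratios are 0.68-0.79 and 0.33-0.48.

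Overall, at 30% prevalence and 10-30% random incompleteness, the shift is about 1 to 3 points. That is smaller than the sampling half-width of about 7 points, but it is systematic. It is larger if components are more prevalent or if missingness tracks weakness. Prevalence, correlation and incompleteness are all assumed, so the direction is firm and the size is not. The change is worth making before analysis and does not undermine the study.

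**What to change.** - For retained assessments with one or two components missing, multiply impute the component scores from the observed components, age, sex and timepoint, then apply the 3-of-5 and 2-of-5 cut-offs.
- Report the frailty percentage with lower and upper bounds (all missing components absent; all present) and a complete-case sensitivity analysis. The bounds matter because imputation relies on missingness being explained by the variables used.
- Tabulate missing components by age and timepoint.
- If the data allow, record when a test could not be done because of the child's physical condition, and score it as abnormal in a sensitivity analysis.
- Reconcile the self-reported fatigue label in the Physical Frailty section and Table 2 with the Fatigue section by naming the PedsQL-MFS score that defines the component at each age. Ages 3-7 have only the proxy score. Using proxy or self-report from age 8 is a judgement for the authors.

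**Cost.** A few sentences in the definition, a modest imputation step and slightly wider intervals. Except perhaps for the reasons tests were missed, no new data are needed. Accrual had closed and analysis was still planned when the article was written.
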